## Insights for the main experimental study

The results of this pilot study provided important insights for the main investigation. In line with former studies [10,11], the Ambiguous Scenarios Task appears suitable for this line of investigation. Participants showed a high level of engagement with the task, and those allocated to the pain modification group showed higher intensity and unpleasantness ratings on the ISSA than those in the benign modification group, typically with medium to large effect sizes. Furthermore, participants in the pain modification group had higher pain-related interpretation bias scores on the test phase of the Ambiguous Scenarios Task compared to those in the benign modification group, with a large effect size. Taken together, this suggests the Ambiguous Scenarios Task with linguistic stimuli is capable of modifying interpretation biases, which in turn affects intensity and unpleasantness ratings for ambiguous somatosensory sensations. Considering the other cognitive paradigms, little difference in interpretation scores were shown between the two modification groups on the Incidental Learning Task, with the results suggesting a lack of learning across participants. Few former studies have used this paradigm to explore pain-related biases, although these found pain-free individuals can learn the association between stimulus type and dot location [55,56]. While it is unknown why learning did not occur in the present pilot study, these former studies used ambiguous facial expressions as opposed to linguistic stimuli. Considering the Sentence Generation Task, a higher proportion of pain-related sentences was generated by the pain modification group than the benign modification group. Although the effect size was small, this nevertheless implies this task may be more suitable for the current line of investigation using linguistic stimuli than the Incidental Learning Task. During the ISSA, 120% and 140% heat thresholds could not be reached for five and two participants respectively due to TSA-II safety limits of 50°C. This indicates that the paradigm requires modification while importantly adhering to safety limits of the equipment.

Based upon these findings and results from the broader literature, the following modifications have been made to the experimental protocol for the main investigation. First, the primary outcome of interpretation of ambiguous somatosensory sensations will be performed immediately following CBM-I, with assessment of post CBM-I cognitive biases performed after this. This will eliminate the possibility that assessing post-CBM-I cognitive biases reduces the training effect. Second, assessments of pain-related attentional bias and memory bias will also be conducted following CBM-I. Pain-related biases in attention (e.g., [57–68]) and memory (e.g., [45,69–74] have been frequently explored by our research group and others across a range of populations and using a range of paradigms, and their inclusion in the protocol will enable an assessment of the inter-relatedness of different forms of cognitive bias as predicted by theoretical models such as the Threat Interpretation Model of Pain [75] and the Integrated Contextual-Functional Framework [76]. Third, due to the small between-groups effect size (*d* =  -0.05) in the pilot study, the Incidental Learning Task will not be included (and which will provide time for assessments of attentional and memory bias). Fourth, in addition to ambiguous hot sensations, an assessment of interpretation of ambiguous cold sensations will also be conducted, as research suggests people are more sensitive to cold stimuli than hot stimuli [77,78], perhaps due to a greater overall density of cutaneous cold thermoreceptors than warm receptors [79]. Fifth, research has suggested intolerance of uncertainty is associated with higher experimental pain intensity ratings [80]. The Intolerance of Uncertainty Scale-12 Item [81] measure will therefore be added to the questionnaire battery in order to explore associations between intolerance of uncertainty and interpretation of ambiguous somatosensory sensations.

## Protocol for main experimental study

The protocol for the main experimental study is detailed here. Methods and procedures that remain identical to the pilot study will be outlined briefly, while all modifications will be discussed in detail.

### Aims and hypotheses

The primary aim of the main experimental study is to investigate the effects of pain-related CBM-I on the interpretation of ambiguous somatosensory stimuli in healthy, pain-free individuals. The secondary aim is to investigate the effects of CBM-I on patterns of pain-related interpretation, attentional and memory bias. A between-groups design will be implemented, randomising healthy participants to benign CBM-I or pain CBM-I conditions. It is hypothesised that:

Participants in the pain modification group will interpret somatosensory stimuli at levels around the pain threshold as more intense and unpleasant than participants in the benign modification group.Participants in the pain modification group will have higher levels of pain-related interpretation bias for ambiguous words and scenarios, as compared to the benign modification group. This is operationalised by:a. In the Ambiguous Scenarios Task, participants in the pain modification group will be more likely to interpret ambiguous scenarios as pain-related, as compared to participants in the benign modification group.b. In the Sentence Generation Task, participants in the pain modification group will generate more pain-related sentences than participants in the benign modification group.Participants in the pain modification group will have higher levels of pain-related attentional and memory biases bias than participants in the benign modification group.

### Primary and secondary outcomes

The primary outcomes in this study are pain intensity and unpleasantness for ambiguous somatosensory sensations as assessed via the ISSA paradigm. Secondary outcomes are (i) pain-related interpretation biases for ambiguous words and scenarios as assessed via the Ambiguous Scenarios Task and Sentence Generation Task respectively, (ii) pain-related attentional and memory biases as assessed via the visual-probe task and surprise free-recall task respectively, and (iii) anxiety (State-Trait Anxiety Inventory), depression (Beck Depression Inventory-II), anxiety sensitivity (Anxiety Sensitivity Index-3), somatosensory amplification (Somatosensory Amplification Scale), pain catastrophising (Pain Catastrophising Scale), intolerance of uncertainty (Intolerance of Uncertainty Scale-12 Item), and handedness (Edinburgh Handedness Questionnaire – Short Form).

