### Self-report measures

The following self-report measures will be administered in a newly randomised order for each participant: Anxiety Sensitivity Index-3 (ASI-III) [23]; Somatosensory Amplification Scale (SSAS) [32]; Fear of Pain Questionnaire– III (FoP-III) [34]; Pain Catastrophising Scale (PCS) [37]; Beck Depression Inventory-II (BDI-II) (Beck, Steer, & Carbin, 1988); Intolerance of Uncertainty Scale-12 Item (IUS-12) [81]; State-Trait Anxiety Inventory (STAI) [20]; Edinburgh Handedness Questionnaire – Short Form [40]. A demographic questionnaire will also be administered assessing sex, occupation, level of education, personal pain experiences (including number of headache days per month, for females their current phase of menstrual cycle) and prevalence of chronic pain among close relatives. The IUS-12 [81] is new for this main experimental study. This scale includes 12 items assessing an individual’s inclination to find uncertain situations unpleasant. Items are rated on a five-point scale ranging from 1 (Not at all characteristic of me) to 5 (Entirely characteristic of me). Total scores range from 12 to 60, with higher scores indicating greater intolerance of uncertainty. The IUS-12 has demonstrated excellent internal consistency (.91) [81] and acceptable test-retest reliability ((*r* = .77) [83]). Overall, the questionnaires will take approximately 25 minutes to complete.

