### Procedure

The procedure for this study is shown in Fig 4. Participant ID numbers will be randomly assigned to the benign or pain modification group before data collection begins. After having read the information sheet and signed the consent form, participants will first complete the questionnaire battery. Following this, participants will complete the pain-threshold measurement task to assess their hot and cold pain thresholds. Next, participants will complete the Ambiguous Scenarios Task aiming to modify their biases towards pain-related or benign interpretations of ambiguous stimuli, according to their randomised group. Immediately following this, participants will complete the Interpretation of Ambiguous Sensation Task. All participants will then complete the battery of cognitive bias tasks. The test phase of the Ambiguous Scenarios Task will be completed first. The order of the sentence generation task and visual-probe task will be randomised and counterbalanced across participants, with the free recall memory bias task conducted last. Lastly, those randomised to the pain modification condition will complete the bias repair task. Participants will complete the study in a single session lasting approximately two hours minutes. Following completion of the study, participants will be thanked and debriefed. The entire experiment will take approximately 120 minutes to complete.

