Descriptive statistics will be computed for demographic characteristics, self-report measures (scored according to their instructions), cognitive bias task scores (Ambiguous Scenarios Task test phase, Sentence Generation Task, Visual-Probe Task and free recall task) and responses on the Interpretation of Ambiguous Somatosensory Sensations Task. Differences between the benign and pain modification groups will be conducted using independent samples *t*-tests and mixed-design ANOVAs where appropriate. Should any statistically significant differences be observed between groups on demographic or self-report measures, analyses will be conducted controlling for these (e.g., Analysis of Covariance). Pearson’s correlation coefficients will be conducted between outcomes on the self-report measures, cognitive bias scores and interpretation of ambiguous sensations ratings. As thermal pain sensitivity is associated with age (e.g., [88–90]), Pearson’s correlation coefficients will also be computed between age and interpretation of ambiguous sensations ratings. Should these be statistically significant, then age will be controlled for as a covariate where appropriate in the statistical analyses. The moderating effects of visual imagery and intolerance of uncertainty on the association between group and interpretation bias scores from the Ambiguous Scenarios Task will be investigated using linear multiple regression models. Similarly, linear multiple regression models will be used to test the effect of group on interpretation bias measures while controlling for other variables that differ between groups.

Data from the Ambiguous Scenarios Task, Sentence Generation Task and ISSA will be processed as discussed above for the pilot study. The only difference is that for the Sentence Generation Task, two raters will independently and blindly categorise participant response sentences as either pain-related (e.g., *He had a pressing pain in his head*) or benign (e.g., *The boy was pressing the buttons in the lift*). The initial inter-rater agreement will be computed, and any disagreements between raters will be discussed in order to reach consensus (involving a third independent member of the research team if necessary).

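### Seven self-report instruments, including handedness, are listed as secondary outcomes although the procedure describes them only before CBM-I training, so they cannot reflect its effect

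*Protocol article*

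**What the plan says.** Under Primary and secondary outcomes, the third group of secondary outcomes begins "iii) anxiety (State-Trait Anxiety Inventory), depression (Beck Depression Inventory-II), anxiety sensitivity (Anxiety Sensitivity Index-3), somatosensory amplification (Somatosensory Amplification Scale". In full it covers the State-Trait Anxiety Inventory (STAI), Beck Depression Inventory-II (BDI-II), Anxiety Sensitivity Index-3 (ASI-3), Somatosensory Amplification Scale (SSAS), Pain Catastrophising Scale (PCS) and Intolerance of Uncertainty Scale (IUS-12). It closes with "and handedness (Edinburgh Handedness Questionnaire – Short Form".

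The main-study Procedure sets the order. After consent, "participants will first complete the questionnaire battery". The heat and cold thresholds follow. Then: "Next, participants will complete the Ambiguous Scenarios Task aiming to modify their biases towards pain-related or benign interpretations of ambiguous stimuli". The somatosensory assessment (ISSA) comes straight after training. After that, "All participants will then complete the battery of cognitive bias tasks". The pain group ends with the bias repair task. The visit structure is also fixed: "Participants will complete the study in a single session".

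The main-study Data reduction and analytic plan gives the self-report scores other roles. They are described, they are correlated with the bias scores and ISSA ratings, and they can trigger adjustment: "Should any statistically significant differences be observed between groups on demographic or self-report measures, analyses will be conducted controlling for these". Intolerance of uncertainty is also a moderator of the relation between group and interpretation bias.

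**The concern.** An outcome of an intervention has to be measured after it. As the procedure is written, every score in the third group is fixed before the participant meets the training material. Under randomisation, the two groups can then differ on these scores only by chance.

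The outcome list and the analytic plan also assign the same variables incompatible roles. A measure taken twice can serve as both a baseline covariate and an outcome. A measure taken once, before training, cannot.

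What is at stake is what may be reported as a result of CBM-I. The analytic plan does compare the groups on the self-report measures. Under the label in the outcome list, that one comparison becomes both a secondary-outcome test and the trigger for covariate adjustment.

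**Working it through.** **1. Order of events against the outcome list (main study).**

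| Step | Activity | Listed as |
|---|---|---|
| 1 | Questionnaire battery | Secondary outcome, group (iii) |
| 2 | Heat and cold pain thresholds | not listed |
| 3 | CBM-I training | intervention |
| 4 | ISSA ratings | Primary outcome |
| 5 | Ambiguous Scenarios test phase, Sentence Generation, Visual-Probe, free recall | Secondary outcomes (i) and (ii) |
| 6 | Bias repair (pain group only) | not listed |

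Groups (i) and (ii) and the primary outcomes fall after step 3. Group (iii) falls before it.

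**2. Could a second administration be implied?** The flowchart is not shown, so this was checked from the text. The section on insights from the pilot lists five modifications. One adds the IUS-12 to the battery; none adds a post-training questionnaire. The stated durations are: questionnaires 25 minutes, thresholds 10, Ambiguous Scenarios Task 20 (pilot figure), ISSA 20, Sentence Generation 15 (pilot figure), Visual-Probe 15, recall 2.

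- Sum: 25 + 10 + 20 + 20 + 15 + 15 + 2 = 107 minutes, against about 120 stated, before consent, bias repair and debrief.
- With a second full battery: 107 + 25 = 132 minutes.

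A full repeat would not fit. A shorter one cannot be strictly excluded, but none is described.

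**3. Consistency with the aims.** The secondary aim under Aims and hypotheses covers interpretation, attentional and memory bias. None of the hypotheses concerns a questionnaire. The pilot section on self-report measures says that handedness was collected to confirm hand dominance for sensory testing, which makes it a set-up variable.

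**4. Completeness of the list.** The main-study Self-report measures section introduces the battery ("The following self-report measures will be administered in a newly randomised order for each participant") and includes the Fear of Pain Questionnaire. The outcome list omits it.

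**5. Size of the reporting risk.** Count STAI state and trait separately, plus BDI-II, ASI-3, SSAS, PCS, IUS-12 and handedness: eight scores. Each is tested at .05 two-sided, with no true difference because all precede training.

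- Independent tests: 1 − 0.95^8 = 1 − 0.663 = 0.337, about 34%.
- Without handedness: 1 − 0.95^7 = 0.302, about 30%.
- Correlated scales: the documents give no correlations between scales, so these are assumed. With seven jointly normal scores equally correlated at ρ and handedness independent, the chance is about 31% at ρ = .3, 27% at ρ = .5 and 22% at ρ = .7.

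**6. What a chance difference can look like.** In the pilot the questionnaires also preceded training. Table 2 gives ASI-3 total 13.22 (SD 5.63) in the benign group and 30.00 (SD 8.03) in the pain group, n = 9 each.

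- Pooled SD = √[(5.63² + 8.03²)/2] = 6.93.
- d = (30.00 − 13.22)/6.93 = 16.78/6.93 = 2.42.
- t(16) = 2.42 × √(9/2) = 5.13, p ≈ .0001.

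This is an extreme row of a 16-row table. It shows that a large difference can be present before training; it does not estimate how often that happens.

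**7. Sample size.** With f = 0.244, alpha .05, numerator df 1 and two groups, the noncentral F test gives power 0.7977 at N = 133 and 0.8006 at N = 134. The stated 134 is reproduced and does not depend on how the questionnaires are classified.

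**The case against.** The strongest reply is that this is loose wording with little effect on the analysis. No aim or hypothesis concerns these scales. The analytic plan already handles them mainly as baseline variables, and it too uses the word outcomes loosely for self-report scores in the correlation analyses. Handedness in the list suggests that the authors meant measures. The pilot presents Table 2 as descriptive statistics, with no test and no claim of an effect. All of this stands, and it limits the consequence.

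A reader might infer that the trial is committed to reporting pre-training differences as effects of CBM-I, so that any significant one is a false finding by construction. The documents do not support that. No passage plans such an interpretation, and a baseline difference becomes a false finding only if it is read as an effect of training.

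The 34% is likewise not an expected rate. It assumes independence, which is implausible among anxiety, depression and catastrophising scales, and it counts handedness, which nobody would read as an effect.

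The reply does not rescue the outcome list itself. That section is the formal statement of outcomes, it sets these scales beside the bias tasks, and the analytic plan does compare the groups on them.

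One could also say that significance-triggered adjustment is a separate issue from the label. It is separable, but both concern the role of the same scores and can be settled in the same edit.

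**Conclusion.** The point holds as an error of classification. Group (iii) of the secondary outcomes is wrong as written, because the procedure places these instruments only before training and the rest of the protocol uses them as covariates, correlates and a moderator. The primary outcomes, the hypotheses and N = 134 are unaffected.

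The practical risk is that a chance baseline difference is reported as a secondary-outcome result. Its probability is at most about 34% for at least one of eight scores, and about 22% to 31% under the assumed correlations of .7 to .3. These figures are illustrative.

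The conclusion rests on one reading: that the battery is given once. The text supports this, but the flowchart could not be seen. If a post-training administration is intended, the list may be partly right and the procedure incomplete. That would still not make handedness an outcome of CBM-I.

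**What to change.** - Remove group (iii) from the secondary outcomes. List these measures, with the Fear of Pain Questionnaire, as baseline characteristics, covariates or moderators. Intolerance of uncertainty already has a stated moderator role.
- If any scale is to be repeated after training, say so in the Procedure, name the scale, and keep only the post-training score as an outcome.
- State that between-group differences on pre-training scores will not be interpreted as effects of CBM-I.
- Choose adjustment covariates in advance by their expected relation to the outcome, in place of the rule that waits for a significant baseline difference. STAI-State is one candidate: the pilot's Correlational analyses section gives r = .72, .75 and .77 with unpleasantness at 60%, 80% and 100% of threshold. That rests on 18 participants, so it supports the choice without settling it.

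The cost is a wording change in the outcome list and the analytic plan, and a registry update if the outcomes were registered in this form, which cannot be seen from the document. No change to sample size, assessments or visit length is needed unless a repeat administration is added.

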### Participants

Ethical approval has been granted by University of Southampton Research Ethics Committee (ERGO ID: 92317). Eligibility criteria for inclusion are: (i) aged 18–50 years; (ii) normal or corrected to normal vision; and (iii) fluency in the English language. Exclusion criteria are: (i) diagnosis of any type of chronic pain or psychiatric condition; (ii) currently experiencing pain; or (iii) diagnosis or knowledge of any reading difficulties. Participants will be recruited using social media, word-of-mouth, and the website SONA which is used to recruit undergraduate psychology students at the University of Southampton. BSc Psychology students at the University of Southampton will receive partial course credit for participating. A power analysis was conducted using G*Power [82] to determine suitable sample size for an ANOVA, with a medium effect size based on the pilot study which revealed many of the intensity and unpleasantness ratings between benign and pain modification groups were of medium to large effect (effect size *f* =  0.244, α error probability =  0.05, power (1 – *β* error probability) =  0.80, numerator degrees of freedom =  1, and number of groups =  2). This indicates a sample size of 134 is required for these conditions to be met. The start date for this study is 1^st^ June 2024 and the planned end date as registered with the University of Southampton Research Ethics Committee is 1^st^ May 2026.

### Self-report measures

The following self-report measures will be administered in a newly randomised order for each participant: Anxiety Sensitivity Index-3 (ASI-III) [23]; Somatosensory Amplification Scale (SSAS) [32]; Fear of Pain Questionnaire– III (FoP-III) [34]; Pain Catastrophising Scale (PCS) [37]; Beck Depression Inventory-II (BDI-II) (Beck, Steer, & Carbin, 1988); Intolerance of Uncertainty Scale-12 Item (IUS-12) [81]; State-Trait Anxiety Inventory (STAI) [20]; Edinburgh Handedness Questionnaire – Short Form [40]. A demographic questionnaire will also be administered assessing sex, occupation, level of education, personal pain experiences (including number of headache days per month, for females their current phase of menstrual cycle) and prevalence of chronic pain among close relatives. The IUS-12 [81] is new for this main experimental study. This scale includes 12 items assessing an individual’s inclination to find uncertain situations unpleasant. Items are rated on a five-point scale ranging from 1 (Not at all characteristic of me) to 5 (Entirely characteristic of me). Total scores range from 12 to 60, with higher scores indicating greater intolerance of uncertainty. The IUS-12 has demonstrated excellent internal consistency (.91) [81] and acceptable test-retest reliability ((*r* = .77) [83]). Overall, the questionnaires will take approximately 25 minutes to complete.

